# Clinical Trial Protocol

## 1. Full Title of the Clinical Trial

A randomized controlled trial to evaluate effect of a structured rehabilitation exercise on facedown posture-related musculoskeletal pain after retinal surgery

## 4. Name and title of research drug/medical device managing pharmacist/device manager.

Not applicable.

## 5. The code name of the research drug or medical device, the general name of the main therapeutic chemical component (raw materials in the case of medical devices) and their quantity, formulation

(shape/structure in the case of medical devices), etc.

Not applicable.

## **6. Research sponsor name and address**

Not applicable. This is an investigator initiated trial.

## **7. Background and purpose of the study**

### **7.1 Background and rationale**

Macular hole surgery and retinal detachment surgery frequently involve intraocular tamponade. Intraocular tamponade is a method of injecting fillers into the eye during vitreoretinal surgery to use the buoyancy and provide force to press the retina and promote reattachment of retina and macular hole occlusion. Facedown positioning, posture with the pupil facing the floor, lying on the stomach or sitting with the head bent deeply, is recommended after the surgery so that the buoyancy of the fillings in the eye works properly on macula. It is recommended to maintain the posture 3 to 10 days depending on the patient's condition.

Spending most of the time maintaining facedown posture, many patients experience musculoskeletal pain on their back neck, shoulder, and lower back. Patients with long-term posture restrictions in bed also complain of psychological isolation and boredom. Maintaining facedown posture could be a more difficult experience than the surgery itself to patients and discomfort caused by prone posture may affect the outcome of retinal surgery by lowering patient compliance after surgery.

Most of the vitreoretinal surgeons paid attention only to the outcome of the surgery, and the patient's discomfort caused by facedown posture was not greatly noticed previously. Currently, the intervention method for patient's pain complaint on musculoskeletal discomfort is limited. There has been no structured rehabilitation exercise proposed in the previous literature, and no study evaluated the effect of structured exercise therapy for facedown posture-related musculoskeletal pain.

Department of Ophthalmology and Department of physical and rehabilitation medicine, together, devised a novel structured exercise program for alleviation of musculoskeletal pain in back neck, shoulder, and lower back caused by facedown posture after retinal surgery. The investigators expect the rehabilitation exercise program to reduce musculoskeletal pain, increase subjective satisfaction after surgery, and maximize the effect of prone position (buoyancy pressing macula) by relieving posture related pain and

increasing posture maintenance time.

## **7.2 Study purpose**

The objective of this study is to evaluate efficacy of the structured exercise program for reduction of musculoskeletal pain in patients who maintain a facedown posture with their pupils facing the floor after retinal surgery.

## **8. Target disease**

- Retinal detachment (rhegmatogenous and tranctional)
- Macular hole

## **9. Selection criteria, exclusion criteria, target number of subjects and their basis**

### **9.1 Subject selection criteria**

- (1) Patients 18 years of age or older who have been diagnosed with retinal detachment (rhegmatogenous retinal detachment, traction retinal detachment) or macular hole and who are scheduled for prone position after retinal surgery.
- (2) Patients who signed the provided consent form.

### **9.2 Subject exclusion criteria**

- (1) Patients with pre-existing musculoskeletal disorder.
- (2) patients with poor visual acuity in the opposite eye (best-corrected visual acuity less than 20/200 by snellen chart) making patients hard to get the exercise training.
- (3) Patients with posture prescriptions other than the prone position

### **9.3 Criteria for dropout**

- (1) Patients who stop rehabilitation exercise therapy in the middle.
- (2) Patients whose exercise performance rate is significantly low. Patients who performed less than 2 times out of 3 times a day.
- (3) Patients discharged from the hospital before the postoperative day 3 due to personal circumstances.

(4) Patients who use personal massage device.

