#### **9.4 Sample size calculation**

No relevant studies have previously described the effect of structured exercise on FDP related pain. There has been only one study that evaluated FDP related pain quantitatively. A randomized controlled study performed by Adachi et al. reported the effects of aromatherapy massage on FDP related pain after vitrectomy. Based on the clinical assumption that structured exercise program would have comparable or greater effect on FDP related pain, we conducted a sample size calculation using data from the previous report. We conducted a sample size calculation expecting an effect size of 0.9 based on post-treatment back pain score in aromatherapy group and control group of the previous study. The estimated sample size was 32 patients per group to detect differences between two groups at 90% power and a significance level of 0.05. Considering a 10 % loss to follow-up, we are aiming to recruit 35 patients in each arm.

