## 11. Research method

This study is for patients who are going to be prescribed facedown posture after retinal surgery.

Participating the study or not will not influence the clinical decision and surgical procedure, but only a pain assessment in the back neck, shoulder, and lower back will be additionally performed every day after the surgery for the study participants. Those who are assigned to the exercise group will additionally be instructed for a structured exercise program designed to keep the prone posture easily and to relieve musculoskeletal pain. The exercise group will be trained by an exercise therapist. All inpatient care and surgical procedures other than learning and performing rehabilitation exercise will be the same in both study groups.

| Control group                                                                                      | Exercise group                                                                                                                                                              |
|----------------------------------------------------------------------------------------------------|-----------------------------------------------------------------------------------------------------------------------------------------------------------------------------|
| After surgery, take and maintain facedown posture without getting additional training or exercise. | After surgery, subjects will be trained for a structured exercise routine by an exercise therapist and perform the exercise according to the instruction three times a day. |
| Pain assessment will be performed every day after surgery.                                         |                                                                                                                                                                             |

All patients scheduled for vitreoretinal surgery for macular hole or retinal detachment is going to be admitted to the hospital the day before surgery (day 1). On the day 1, every patients will be evaluated for their eligibility, and those who are eligible candidates will be provided with information about the trial and invited to participate. They will be given enough time to consider their decision and the opportunity to ask questions. After informed consent is obtained, subjects will be randomized.

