### 14. Outcome measures and statistical analysis

#### 14.1. Primary outcome

Pain score measured by numeric rating scale at back neck, shoulder, and lower back on the postoperative day 3. Numeric rating scale is a score that measures pain. If there is no pain, it is marked as 0, and if the pain is the worst possible pain, it is measured as 10.

[figure not shown]

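### Two dropout rules in Section 9.3 can be met only in the exercise arm; if they govern data collection or analysis, the POD 3 comparison is no longer between randomised groups

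*Protocol*

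**What the plan says.** Section 9.3 lists four ways in which a patient becomes a dropout:

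- Rule (1): "Patients who stop rehabilitation exercise therapy in the middle".
- Rule (2): "Patients whose exercise performance rate is significantly low. Patients who performed less than 2 times out of 3 times a day".
- Rule (3): "Patients discharged from the hospital before the postoperative day 3 due to personal circumstances".
- Rule (4): "Patients who use personal massage device".

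Section 11 describes the control arm as follows: "After surgery, take and maintain facedown posture without getting additional training or exercise". On timing, the same section says: "After informed consent is obtained, subjects will be randomized". That is day 1, the day before surgery; exercise begins after surgery on day 2.

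The primary outcome (Section 14.1) is: "Pain score measured by numeric rating scale at back neck, shoulder, and lower back on the postoperative day 3". Section 11 keeps patients in hospital until POD 3, and the schedule has pain scored on the surgery day and on each day to POD 3.

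Section 14.3 names a t-test or rank sum test at 0.017 per site. It does not say who is analysed. The attrition allowance in Section 9.4 reads: "Considering a 10 % loss to follow-up, we are aiming to recruit 35 patients in each arm".

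**The concern.** Rules (1) and (2) act after randomisation, depend on behaviour during treatment, and can be met in one arm only. Randomisation makes the arms comparable as allocated. It does not make the adherent part of one arm comparable with the whole of the other.

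If the dropout label means that a patient is no longer scored or no longer analysed, the exercise arm is filtered on something that may be related to pain, which is the outcome. The result could then show less pain with exercise when the programme does nothing, and patients who stopped because the exercise hurt would leave the result. Such a comparison would not serve the aim in Section 7.2, which is to evaluate the efficacy of the programme.

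The loss would also be avoidable. A patient who skips exercise but is still in hospital on POD 3 can give the primary outcome as easily as anyone else.

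**Working it through.** **The plan's own figure.** Section 9.4 gives 32 per group for effect size 0.9, 90% power and alpha 0.05. A two-sided t-test needs 26.94, so 27. Dividing by 0.864, the minimum asymptotic relative efficiency of the rank sum test, gives 26.94/0.864 = 31.2, so 32, which matches. For attrition, 32 × 1.1 = 35.2 and 32/0.9 = 35.6; the stated 35 is close to both. These figures are not in dispute. The 10% allowance is described only as loss to follow-up. It comes to 3.5 of 35 patients in each arm.

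**Which arm can meet each rule**

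| Rule | Exercise | Control |
|---|---|---|
| (1) stops exercise | yes | no |
| (2) fewer than 2 of 3 daily sessions | yes | no |
| (3) discharged before POD 3 | yes | yes |
| (4) massage device | yes | yes |

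**Size of the possible bias.** The documents give neither a non-adherence rate nor its correlation with pain, so both are assumptions. Take pain (in SD units) and a latent adherence score as jointly normal, with correlation r between pain and non-adherence and no true treatment effect. Remove the least adherent share f of the exercise arm. The expected shift in that arm's mean, in favour of exercise, is

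shift = r × φ(c)/(1 − f), with c = Φ⁻¹(f).

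- f = 10%: φ(−1.282)/0.9 = 0.1755/0.9 = 0.195. Shift 0.06 (r = 0.3) to 0.10 (r = 0.5).
- f = 20%: φ(−0.842)/0.8 = 0.280/0.8 = 0.350. Shift 0.105 to 0.175; 0.10 to 0.17 when exactly 7 of 35 are removed.
- f = 30%: φ(−0.524)/0.7 = 0.348/0.7 = 0.497. Shift 0.15 to 0.25; 0.14 to 0.23 when exactly 10 of 35 are removed.

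Simulated null trials (35 randomised per arm, two-sided t-test at 0.05/3, exercise arm only filtered) give this per-site type I error:

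| Removed | r = 0 | r = 0.3 to 0.5 |
|---|---|---|
| 10% | about 1.7% | about 2.0–2.8% |
| 20% | about 1.7% | about 2.5–4.5% |
| 30% | about 1.7% | about 3.4–7% |

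Removing an exact count or everyone below a threshold changes these by up to about half a percentage point. With all 35 v 35 kept, the error stays near 1.7% throughout.

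**Power.** For d = 0.9 at two-sided 0.05/3, the t-test has 90.2% power with 35 v 35, 86.9% with 32 v 32 and 85.8% with 28 v 35. The smaller number of patients is therefore a minor part of the problem; the selection is the major part.

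**Power if everyone is kept.** If a share f of the exercise arm gains nothing, the average effect is 0.9 × (1 − f): 0.81 at 10% and 0.72 at 20%. With 35 per arm at 0.05/3, power is 82.2% and 71.0%.

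**The case against.** The strongest reply is that Section 9.3 says only who counts as a dropout. It does not say that their pain scores go uncollected or are thrown away, and Section 14.3 names no analysis population. A statistical analysis plan that is not at hand may keep them. This stands in part. A reader might infer that the protocol already excludes these patients from the analysis; the text does not go that far, so the point is conditional. It still concerns a rule that the protocol states, not a detail left for later. An analysis plan could keep these patients, but it could not recover POD 3 scores that were never taken because someone was recorded as a dropout.

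A second tempting reading is that the rules certainly favour exercise. The documents do not establish this. Section 7.1 links discomfort to lower compliance, but in the setting of facedown posture, not exercise. If patients with little pain skip sessions because they see no need, the shift reverses. Rule (4) can act in either arm; if controls in pain use massage devices more often, removing them works against exercise.

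Third, the only attrition figure in the protocol is 10%, and at that level the distortion is modest. Even at 20% removed, 0.10 to 0.17 SD is 11% to 19% of the planned 0.9 (0.10/0.9 and 0.17/0.9), so most of a true effect of that size would survive. This is fair. But the 10% is for loss to follow-up, and nothing in the protocol limits exercise dropouts to that level.

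Finally, the schedule marks three daily sessions on the surgery and discharge days, and a reader might infer that patients would become dropouts for logistical reasons. Section 9.3 does not say whether the threshold applies to each day, to partial days or to an average. That is an ambiguity to clear up, not evidence that it would happen.

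**Conclusion.** The point holds in conditional form. Rules (1) and (2) can be met only in the exercise arm and only after randomisation, and no part of the protocol retains the patients who meet them. If the rules govern data collection or analysis, the primary comparison is no longer a randomised one.

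The size depends on assumed inputs. For 10% to 30% removed and a correlation of 0.3 to 0.5, the shift under no true effect runs from about 0.06 to 0.23–0.25 SD, and the per-site type I error from about 2.0% to 7%, against 1.7% nominal. With zero correlation there is neither shift nor inflation. A bias towards exercise is the expected direction, not a demonstrated one. The rule should be changed whichever way the bias runs, because the trial's own data could not show its direction once these patients are no longer scored.

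**What to change.** - Reword Section 9.3 so that rules (1) and (2) define non-adherence, not dropout, and state how the 2-of-3 threshold is counted across days and partial days.
- State that NRS scores at all three sites are collected to POD 3 in every randomised patient, whatever their adherence. Patients who leave hospital early under rule (3) may have truly missing scores and should be reported as such.
- State that the primary analysis includes all randomised patients as allocated.
- Report adherence descriptively, and use the adherent subset only for a labelled sensitivity analysis.

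The change adds no visits for patients who stay to POD 3, since daily scoring is already scheduled, and leaves clinical care as it is. The real cost is a smaller estimated effect and lower power: about 82% or 71% at 0.05/3 with 35 per arm if 10% or 20% of the exercise arm gain nothing, against 90% with full benefit. If the sponsor wants to hold 90%, the t-test requirement of 34.8 per arm at d = 0.9 scales roughly to 34.8/0.9² = 43 or 34.8/0.8² = 54 evaluable patients per arm. These figures rest on the same assumed non-adherence rates.

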**<Facedown Exercise>**

- Arms and Legs Exercises in a Bed Position
- Exercising in a four-legged position lying on the bed (back stretch)
- Walking in place from a prone position using a walker

After surgery, the pain score in numeric rating scale will be evaluated immediately after the surgery. The patients will perform the trained posture and exercise three times daily, and the exercise therapist will revisit on the postoperative day 1 to give feedback on posture and exercise. The pain score at the back neck, shoulder and lower back will be evaluated on the postoperative day 1, 2, and 3. There will be no difference in the treatment process other than using rehabilitation exercise therapy during the prone period. Patients will stay in the hospital until the postoperative day 3 and then be discharged. The trial will end on the day 5 (postoperative day 3) as the patients discharged from the hospital.

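### Leaving hospital before postoperative day 3 ends data collection, so an obtainable primary pain score goes uncollected (minor)

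*Protocol*

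**What the plan says.** Protocol section 9.3, item (3), counts as dropouts "Patients discharged from the hospital before the postoperative day 3 due to personal circumstances". The item is not limited to one arm.

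The primary outcome in section 14.1 is "Pain score measured by numeric rating scale at back neck, shoulder, and lower back on the postoperative day 3". The scale is described by its two ends: "If there is no pain, it is marked as 0, and if the pain is the worst possible pain, it is measured as 10". No examination or device is named, and the text does not say whether the number is spoken or written.

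Section 11 plans one stay for everyone: "Patients will stay in the hospital until the postoperative day 3 and then be discharged". It then closes follow-up: "The trial will end on the day 5 (postoperative day 3) as the patients discharged from the hospital". Neither section 11, its schedule table nor section 12 describes any contact after discharge.

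On the length of posturing, section 7.1 says: "It is recommended to maintain the posture 3 to 10 days depending on the patient's condition". The schedule table also marks facedown posture on POD 3.

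**The concern.** Item (3) ties the end of data collection to leaving the ward, although the trial's question is about pain while posturing. A patient who goes home on POD 1 or 2 may still be posturing on POD 3 and could still say how much the neck, shoulder and lower back hurt. Read together, sections 9.3 and 11 mean nobody asks.

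A statistical analysis plan cannot repair this. It can define analysis sets and methods for missing data, but it cannot recover a score that the protocol does not collect.

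Two things are at stake. The smaller is precision, because each early leaver removes a primary observation. The larger in principle is comparability. Discharge happens after randomisation, participants know their arm (section 9.6), and the undefined term personal circumstances could include leaving because posturing is uncomfortable. If leaving were related to both arm and pain, the patients left for comparison would no longer be the randomised groups.

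**Working it through.** **1. Is the score lost, and need it be?**

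- Time point: the primary score is due on POD 3 (14.1), and item (3) applies to anyone discharged before that day (9.3). Every patient caught by the rule is caught before the primary assessment.
- Route: follow-up ends at discharge (11) and no later contact is planned, so the score is not collected.
- Relevance at home: posture is recommended for 3 to 10 days (7.1), so POD 3 pain still bears on the trial's question.
- Feasibility: a 0 to 10 self-rating with both ends defined in words needs no hospital equipment. That it can be taken by telephone is my inference.
- Intervention: the therapist's visits are before surgery and on POD 1 (11), and the schedule table lists a brochure and movie clip. No therapist visit is planned for POD 2 or 3.

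**2. The plan's own sample size**

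Inputs from section 9.4: "expecting an effect size of 0.9 based on post-treatment back pain score", "at 90% power and a significance level of 0.05", 32 per group, 10% loss, 35 per arm. Sidedness is not stated; I assume two-sided.

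- Normal approximation: n = 2(1.960 + 1.282)² / 0.9² = 25.9, so 26.
- Exact t-test: 26.94, so 27.
- Wilcoxon rank sum, dividing the t-test n by the minimum relative efficiency 0.864: 26.94 / 0.864 = 31.18, so 32. This reproduces the stated figure.
- Allowance for loss: 32 / 0.9 = 35.6, so 36. The stated 35 is one lower.

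**3. Power if some patients leave early**

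The protocol gives no early-discharge rate. Assumption: 2 to 4 of 35 per arm (6% to 11%), leaving 33 to 31. Two-sided t-test power comes from the noncentral t distribution with 2n − 2 degrees of freedom and noncentrality 0.9 × √(n/2). The two levels are the 0.05 of section 9.4 and the Bonferroni level 0.05/3 of section 14.3.

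| Scored per arm | Noncentrality | Power at 0.05 | Power at 0.05/3 |
|---|---|---|---|
| 35 | 3.76 | 96.0% | 90.2% |
| 33 | 3.66 | 95.0% | 88.1% |
| 31 | 3.54 | 93.7% | 85.6% |

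With no other loss, collecting the missing scores could recover at most about 2 points at 0.05 and about 4.5 points at 0.05/3.

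**4. Possible bias, illustration only**

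- Removing a fraction p of an arm whose mean differs by δ SD from those who stay shifts that arm's observed mean by p × δ. If 10% of one arm and 3% of the other left, and leavers differed by 1 SD in the same direction, the contrast would move by 0.10 − 0.03 = 0.07 SD. That is 0.07 / 0.9, about 8% of the assumed effect.
- Extreme case: the patients lost from one arm are exactly those with the highest pain, and scores are normal. The shift is φ(z) / (1 − f), where f is the fraction lost and z its upper cut-point. It equals 0.07 SD at f = 3%, 0.13 SD at 6% and 0.19 SD at 10%. The last is about a fifth of the assumed effect.

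None of these leaving rates or differences is in the protocol.

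**The case against.** The rule can be defended. The design keeps inpatient care the same in both arms apart from the exercise programme (section 11). At home, trial staff no longer observe posture, exercise or massage-device use, the last being itself a dropout criterion. A POD 3 score from home is therefore taken in another setting as well as by another mode. The planned stay runs to POD 3 for everyone, early departures may be rare, and the 10% allowance exists for loss of this kind. All of this stands and limits the severity. It is a reason to label such scores and test sensitivity to them, but not a reason to leave them uncollected.

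Some stronger readings are tempting but lack support:

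- **That the loss is selective.** The rule covers both arms, and the discomfort, isolation and boredom in section 7.1 are linked to posturing, which both arms do. Nothing shows that leaving depends on arm. Items (1) and (2) of section 9.3 concern exercise adherence, can bite only in the exercise arm, and are a clearer source of unequal loss; their weight should not be borrowed here.
- **That the rule seriously damages power.** Power of about 83% at 0.05/3 needs 29 scored per arm, a loss of 6 of 35 (17%), which is beyond the range assumed here. Power below 90% at that level arises chiefly from sizing at 0.05 and testing at 0.017, a separate matter.
- **That patients known to be leaving early are randomised and then removed.** The eligibility criteria do not require a stay to POD 3, but nothing shows that such patients exist.
- **That dropouts' earlier scores are discarded.** The protocol does not say so, and analysis sets may be defined in a plan not shown.

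**Conclusion.** The point holds in limited form. As written, sections 9.3 and 11 leave the POD 3 primary scores of early-discharged patients uncollected. The loss is probably avoidable, and it occurs after randomisation in an open-label trial.

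At the assumed 2 to 4 leavers of 35 per arm, the cost in power is about 2 to 4.5 percentage points at 0.05/3 and about 1 to 2 points at 0.05. Bias is possible but neither its size nor its direction can be derived from the protocol; the shifts of 0.07 to 0.19 SD depend entirely on the assumptions stated with them.

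The conclusion rests on two inferences: that the rating can be taken remotely, and that no contact after discharge takes place beyond what is described. Severity is minor. The case for change is that a small avoidable loss can be prevented cheaply.

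**What to change.** In section 9.3, remove item (3) as a ground for ending data collection. In section 11, state that for any patient discharged before POD 3 the remaining pain scores at each of the three sites, POD 3 included, will be sought by telephone on the scheduled day with the same wording. Record the mode of collection and the day of discharge. Include these patients in the primary comparison as randomised, and add a sensitivity analysis that excludes scores taken after discharge. If the analysis sets are defined in a statistical analysis plan, align its wording.

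This changes data collection and analysis only; decisions on discharge and posture are untouched.

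The cost is amended wording in two sections, two extra fields on the case report form, and a few short calls by existing staff. The downside is that a few scores come by a different mode and from a home setting where posture, exercise and massage-device use are not observed.

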## 12. Clinical evaluation items and observation test method

Pre-operative data collection:

- Demographic data
- Laterality
- Comorbid systemic diseases (diabetes mellitus, arterial hypertension, etc.)
- Indication for vitrectomy
- previous history of ocular surgery
- combined cataract surgery
- methods of anesthesia

Post-operative data collection:

- Intraocular fillings (SF6, C3F8, Silicon oil)

- Operative time
- Pain scores measured by numeric rating scale at back neck, shoulder, and lower back
  - Pain scores will be measured on the surgery day and the postoperative day 1, 2, and 3.
- Patient satisfaction questionnaire for exercise group on the postoperative day 3.

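### Making personal massage device use a dropout criterion excludes randomised patients for behaviour plausibly related to the pain outcome, and can bias the day 3 comparison

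*Protocol*

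**What the plan says.** Section 9.3 gives four criteria for dropout. Item (4) reads "Patients who use personal massage device". It carries no condition on arm, on the reason for use or on its extent. The first two items concern the exercise programme and can apply only to the exercise arm: "Patients who stop rehabilitation exercise therapy in the middle" and "Patients who performed less than 2 times out of 3 times a day".

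The primary outcome in section 14.1 is "Pain score measured by numeric rating scale at back neck, shoulder, and lower back on the postoperative day 3". Section 12 sets the measurement times: "Pain scores will be measured on the surgery day and the postoperative day 1, 2, and 3". The schedule in section 11 places randomisation on the day before surgery, so any device use during the prone period comes after it. Section 9.6 states that participants are not blinded.

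Two other statements bear on the point. Section 7.1 gives the expected direction: "The investigators expect the rehabilitation exercise program to reduce musculoskeletal pain". Section 9.4 takes its planning value from a trial that "reported the effects of aromatherapy massage on FDP related pain after vitrectomy", "expecting an effect size of 0.9 based on post-treatment back pain score", and adds 10% for loss, going from 32 to 35 per arm.

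**The concern.** A criterion that acts after randomisation and is linked to the outcome can undo the balance that randomisation provides. Massage of a sore neck, shoulder or back is a natural response to the symptom being scored. If patients with more pain are more likely to use a device, and users are then left out, the upper part of the pain distribution is thinned in both arms. It is thinned more in the arm with more pain. On the protocol's own expectation that is the control arm, so the remaining controls would look better than the controls who were randomised.

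What is at stake is the size of the primary comparison, some power, and the small reserve for loss. The allowance is 35 − 32 = 3 patients per arm, and it must also cover early discharge under item (3) and the exercise-related items.

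**Working it through.** **1. The plan's own figure.** With effect size 0.9, two-sided alpha 0.05 and 90% power, the normal formula gives n = 2(1.960 + 1.282)²/0.9² = 25.9, so 26 per group. The t-test gives 26.94, so 27. Dividing by 0.864, the minimum asymptotic relative efficiency of the Wilcoxon rank-sum test, gives 26.94/0.864 = 31.2, so 32, which matches section 9.4. The protocol does not name its method, so this is one route that reproduces the figure.

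**2. Model for item (4).** From the protocol: true difference 0.9 SD, 35 randomised per arm, significance level 0.05/3 = 0.0167 (section 14.3). Assumed, because the protocol is silent: the overall rate of device use, and how steeply it rises with pain. Day 3 pain is taken as normal with SD 1, mean 0.9 in control and 0 in exercise. The probability of use is logistic in pain with slope b (log-odds per SD), and the intercept is set to give the stated overall rate.

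Difference in means (SD units) among patients who remain when users are left out:

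| Overall use | b = 0 | b = 0.5 | b = 1 | b = 2 |
|---|---|---|---|---|
| 5% | 0.90 | 0.89 | 0.87 | 0.82 |
| 10% | 0.90 | 0.88 | 0.84 | 0.77 |
| 20% | 0.90 | 0.87 | 0.80 | 0.69 |

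**3. Losses by arm.** At 10% use and b = 1, users are 13.5% of controls and 6.5% of exercise patients: 35 × 0.135 = 4.7 and 35 × 0.065 = 2.3 patients. The control figure alone exceeds the reserve of 3.

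**4. Power.** Power = Φ(d/√(1/n_C + 1/n_E) − 2.394). In the same case n_C = 35 − 4.7 = 30.3 and n_E = 35 − 2.3 = 32.7. Leaving out users also narrows the SD, so the standardised d is 0.869. Then 0.869/0.252 − 2.394 = 1.05, and power is about 85% (82% to 87% for b from 2 to 0.5). The same total loss unrelated to pain leaves 31.5 per arm and d = 0.90: 0.90/0.252 − 2.394 = 1.18, or 88%.

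**5. Keeping users in instead.** If the device relieves m SD of pain, the difference becomes 0.90 − m × (0.135 − 0.065). For m = 0, 0.3, 0.5, 0.9 and 1.5 the values are 0.90, 0.88, 0.87, 0.84 and 0.79 (10% use, b = 1). Retention gives the larger difference until m reaches about (0.90 − 0.84)/(0.135 − 0.065) ≈ 0.9 SD. Beyond that, exclusion does.

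**6. A second model on the 0–10 scale.** Assume control mean 5, SD 2.0, exercise mean 5 − 0.9 × 2.0 = 3.2, scores rounded and bounded, and half of those scoring 7 or more using a device. Users are 0.5 × P(Z ≥ 0.75) = 11.3% of controls and 0.5 × P(Z ≥ 1.65) = 2.5% of exercise patients. The mean difference is about 1.76 points with everyone and no device effect, and 1.52 with users excluded (d from 0.89 to 0.83). With users retained and 1, 2 or 3 points of relief it is 1.76 − relief × (0.113 − 0.025), or about 1.67, 1.58 and 1.49.

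**The case against.** The strongest reply is that item (4) has a sensible purpose. Section 9.4 takes its effect size from a massage trial, so the protocol treats massage as acting on this outcome, and section 11 wants care otherwise equal between arms. The item guards against a competing co-intervention. That stands, and it is a reason to keep some text on device use. It does not require dropping users from follow-up or analysis.

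It can also be said that the protocol calls these patients dropouts without saying that their scores are uncollected or unanalysed, and that analysis sets may be fixed in a statistical analysis plan not at hand. This is right, and it makes the point conditional. The loss allowance makes exclusion the natural reading, not a stated one.

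Both models tie use to the day 3 score itself. Real use would come earlier and might concern only one of the three sites, so selection on each endpoint would probably be weaker than shown. Retention also dilutes the difference, and with strong relief it does so more than exclusion. Both remarks stand.

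A reader might infer that the item removes patients because of their pain, mostly controls, and so shrinks the observed effect. The protocol gives no reason, rate or split by arm for device use, so that is inference. A reader might also infer from the data list in section 12 that device use goes unrecorded. The case report form is an appendix that is not shown, and someone must identify users to apply the item at all.

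**Conclusion.** The point holds in conditional form, as a cheap improvement. Item (4) is a post-randomisation criterion plausibly related to the outcome, in a trial whose participants know their arm. If users are left out, the comparison can be biased: probably toward no difference if use rises with pain and controls have more of it, and not at all if use is unrelated to pain. The size cannot be known from the protocol. With about 10% overall use rising with pain, a planned 0.90 SD becomes about 0.77 to 0.88 SD; at 5% use the range is 0.82 to 0.89.

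It would go too far to conclude that section 9.3 as a whole is conservative. Items (1) and (2) act on the exercise arm alone and can work the other way: if they remove 10% of that arm and those removed have more pain, 0.90 SD becomes 0.99 (b = 1) or 1.04 (b = 2). The net direction is undetermined, and the two effects cannot be assumed to cancel.

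**What to change.** State that device use does not remove a patient from follow-up or from the primary analysis. Record it (yes/no, and the day) in both arms at the existing daily pain assessment, keep collecting the day 3 score at all three sites, and analyse all randomised patients as allocated. Report device use by arm, and give the analysis excluding users as a sensitivity analysis only. A sensitivity analysis that gives users their worst earlier score is not advised, because it would favour exercise if controls use devices more. Whether device use is discouraged as a co-intervention is for the investigators to decide; this change does not depend on it.

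The cost is one item at a contact that already takes place and a change to one line of section 9.3. The downside is that users' day 3 scores include any relief from the device, which may also reduce the observed difference. In return, the comparison stays between the groups as randomised, and any imbalance in device use becomes visible.
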